## Abstract

**Background:**

Worldwide, millions of people are suffering from dementia and this number is rising. An index of quality of life (QoL) can describe the impact a disease or treatment has on a person’s wellbeing. QoL comprises many variables, including physical health and function, and mental health and function. QoL is related to masticatory ability and physical activity. Animal studies show that disruption of mastication due to loss of teeth or a soft diet leads to memory loss and learning problems. Since these are common complaints in dementia, it is hypothesized that improvement of masticatory function and normalization of diet consistency can increase QoL in elderly persons suffering from dementia. Therefore, the goal of the present study is to examine whether an increase in masticatory activity, achieved by increased food consistency and enhancement of masticatory function through improved oral health care has a positive effect on QoL, including cognition, mood, activities of daily living (ADL), and circadian rhythm in elderly persons with dementia.

**Methods and design:**

The described study is a prospective longitudinal matched cluster randomized single-blind multicenter study. Participants are elderly persons living in the Netherlands, suffering from dementia and receiving psychogeriatric care. An intervention group will receive improved oral health care and a diet of increased consistency. A control group receives care as usual. Participants will be assessed four times; outcome variables besides QoL are cognition, mood, independence, rest-activity rhythm, blood pressure, and masticatory function.

**Discussion:**

This research protocol investigates the effect of an intervention executed by daily caregivers. The intervention will increase masticatory activity, which is achieved by three different actions, (providing oral health care, increasing food consistency, or a combination of both). There is a certain amount of variety in the nature of the interventions due to local differences in nursing homes. This might be a scientific weakness in the study design; however, a practical implementation of any findings will be subject to the same factors, making this study design clinically relevant.

**Trial registration:**

NTR1561

## Background

Dementia is an umbrella term for a heterogeneous group of neurodegenerative disorders, characterized by functionally disabling, progressive cognitive deterioration [1]. The most prevalent subtypes of dementia are Alzheimer’s disease (AD), frontotemporal dementia (FTD), dementia with Lewy bodies (DLB) and vascular dementia (VaD) [1]. These dementias can present differently; some domains that are affected in one type of dementia are preserved in others [2]. The diagnosis ‘dementia’ should therefore always be based on deficits in more than one cognitive domain [2,3]. Worldwide, almost 36 million people are suffering from dementia and this number is expected to rise to 115.4 million in 2050 [4]. This rise is mainly due to an increase in population of persons aged 60 and over [5], as aging is one of the main risk factors for dementia [6]. Genetic factors play a role as well; the apolipoprotein E (ApoE) ε4 allele is a risk factor for several types of dementia such as AD [7-10]; especially when occurring along with depression [11]. Other risk factors for dementia are female gender, illiteracy/low education, head trauma, lower socioeconomic status (SES) [6], diabetes, depression [7], vascular disorders (e.g., hypertension), environmental stress, and an inactive life style [12].

Quality of life (QoL) is a term used to describe a person’s wellbeing and more specifically, the impact a certain disease or treatment for this disease has on a person’s life [13]. QoL comprises many variables, including physical health (e.g., absence of pain and nausea), physical function (e.g., being independent in the activities of daily living (ADL)), mental health (e.g., absence of fear, agitation and mood disorders), and mental function (e.g., good cognitive function). Having a meaningful pastime and social interactions is another component that is typically included in QoL indexes [14,15]. Using questionnaires to interview caregivers such as relatives or nurses can provide some information regarding a person’s QoL. However, since the observation by such proxies can be different than the patient observation and is influenced by the mood and cognition of the caregiver him/herself [13], using additional methods to assess QoL is preferred. For example, sleep disorders influence a person’s QoL [16], and the sleep pattern and circadian rhythm can easily and objectively be tracked with actigraphy. Similarly, cognition can be measured using neuropsychological tasks. Loss of mental function is one of the more noticeable symptoms of dementia [17], and the diagnosis ‘dementia’ is usually based on cognitive testing [18]. A thorough cognitive screening should therefore also be included when studying QoL in dementia.

As there is no cure for dementia, interventions are aimed at improving the clinical consequences. For example, interventions targeting life style factors, such as increasing physical activity, have been found to improve cognitive measures in healthy elderly [19]. Physical activity interventions targeting elderly persons suffering from dementia may improve cognitive function [20], mood, and QoL [21].

Besides exercise interventions, improvement of, or supplementing the diet can positively influence cognition [22] or reduce the risk of developing cognitive impairments [23]. A ‘good’ diet would comprise fruits, nuts, and vegetables [23]; foods that are typically harder to chew. These foods become more difficult to eat for aging persons, most notably when tooth loss is present [24]. Loss of masticatory function is also associated with increased disability and mortality [25]. Being able to chew properly, therefore, is of utmost importance for elderly persons to maintain a healthy diet and preserve cognition. This is especially the case when they are at risk for, or suffering from, dementia. Unfortunately, many older persons living in a nursing home are completely edentulous [26], and if they have remaining teeth, they are often in need of dental care [27,28]. Offering both oral health care and an improved diet to elderly persons with dementia will most likely improve their health situation and thus, their QoL.

In sum, QoL is a very relevant outcome variable when assessing the results of interventions aimed at elderly persons suffering from dementia. Related mental and physical outcomes such as cognition and independence should be assessed as well to study the effects comprehensively. The study described in this protocol investigates the effect of an intervention aimed at increasing masticatory activity through improving oral health care and increased food consistency, on QoL, including cognition, mood, independence, rest-activity rhythm, and blood pressure in older people with dementia, receiving institutionalized care.

## Methods and design

### Study design

The study has a prospective longitudinal matched cluster randomized single-blind multicenter design. Assignment to either the intervention group or the control group will take place through matched cluster randomization, on a care unit level (i.e. not on an individual level). Participants in the study will be followed for 24 weeks and will be assessed at regular intervals, viz., at baseline, six weeks, twelve weeks, and 24 weeks after baseline. A care organization enrolls two care units, in order to provide matching groups within a single care setting. One group will be a control group and receive care as usual; the other group will be an intervention group. Participants are blind to the intervention. Since receiving training and altering the daily nursing care is part of the intervention, care-givers such as the nursing staff cannot be blind for the intervention. The examiners will be blinded.

### Participants

Participants are elderly persons, aged 65 years and older, diagnosed with dementia and receiving professional psychogeriatric care in a Dutch nursing home or daycare facility. If possible, the subtype of the dementia disorder (e.g., Alzheimer’s disease, vascular dementia, dementia with Lewy bodies, or frontotemporal dementia) will be noted. Exclusion criteria are: a history of psychiatric disorders, including depression, (history of) alcoholism, cerebral traumata, hydrocephalus, and brain tumors. This information will be obtained from the medical records. Another exclusion criteria will be a score on the Mini Mental State Examination (MMSE [29]: a short instrument which assesses global cognition, awareness, and memory), of 25 or higher at baseline. Such a score is contraindicative of dementia [30].

Participants are recruited through psychogeriatric care organizations. After a care organization agrees to participate in the study, all clients and their legal representatives are contacted and invited to participate in the study. They are thoroughly informed about the study, upon which written consent is obtained. Participation is always voluntary.

### Sample size

To calculate the number of participants needed, a power analysis is performed. The primary outcome variable (QoL) is used to calculate the power and a linear time effect is assumed for both intervention and control conditions. A difference on total score of 10 points after 24 weeks is considered clinically relevant. This equals to a difference of 2.5 points per 6 weeks. After running simulations with a known total variance of 300 and a mean score of 80 (pilot data), a sample size of 200 participants (spread over 10 care organizations and 10 participants per care unit) is needed. Allowing for 10% dropout, this means (200 × 10/9 =) 224 participants need to be included in the study.

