### Outcome variables

#### Quality of Life

The primary outcome variable is QoL, assessed with the Qualidem questionnaire [35]. The Qualidem is considered the preferred instrument [36] for rating QoL for elderly persons with dementia and is appropriate for large and small-scale settings [37]. A proxy is asked to rate observable behaviors on a 4-point Likert scale (i.e. ‘never’, ‘rarely’, ‘sometimes’, and ‘often’). Statements are for example: ‘is cheerful’, ‘refuses food’, ‘smiles’, or ‘wants to stay in bed’. For each statement, 0, 1, 2 or 3 points are awarded. The most positive outcome is given the highest point value (e.g., ‘smiles often’ is given 3 points, ‘refuses food often’ is given 0 points). A higher score suggests a higher QoL. The Qualidem score can be divided into several subscales. Not all subscales are appropriate for participants with severe dementia, so only the four subscales recommended for this group [38] will be included; ‘care relationship’ (0-21 points), ‘positive affect’ (0-18 points), ‘restless tense behavior’ (0-9 points), and ‘social isolation’ (0-9 points). The maximal score is 57 points.

As described earlier, QoL comprises many aspects of life. In order to assess this multicomponent aspect of QoL, the following secondary outcome variables are included.

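### The sample size rests on a pilot mean of 80, which cannot occur on a primary outcome capped at 57, so 200 participants is not shown to apply to that outcome

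*Protocol article*

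**What the plan says.** The Sample size section ties the calculation to the primary endpoint: "The primary outcome variable (QoL) is used to calculate the power". The target is "A difference on total score of 10 points after 24 weeks is considered clinically relevant", followed by "This equals to a difference of 2.5 points per 6 weeks". The simulation inputs are "a known total variance of 300 and a mean score of 80 (pilot data". The result is 200 participants, from 10 care organizations with 10 participants per care unit, raised to 224 for 10% dropout.

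The Quality of Life section under Outcome variables defines the same endpoint: "The primary outcome variable is QoL, assessed with the Qualidem questionnaire". On item scoring it says "For each statement, 0, 1, 2 or 3 points are awarded". Because some subscales do not suit severe dementia, it continues "so only the four subscales recommended for this group" will be included: care relationship (0-21), positive affect (0-18), restless tense behaviour (0-9) and social isolation (0-9). It closes with "The maximal score is 57 points".

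The article defines no other quality-of-life total and no rescaling of this one.

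**The concern.** The two sections describe the same variable and cannot both be right. A mean cannot exceed the highest attainable score, so the pilot mean was not computed on the outcome defined for analysis.

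In a linear mixed model the mean itself does not drive the sample size. It matters as evidence of which score the planning figures came from. The variance and the target difference do drive the sample size, and the variance is reported as pilot data together with the impossible mean.

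Two things are at stake. The only published justification for 200 participants may describe a different endpoint. And the 10-point threshold, against which a null or a small effect would be judged, has no confirmed scale: on 0-57 it would be 10/57 = 17.5% of the whole range.

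**Working it through.** **Inputs.** From Sample size: mean 80, total variance 300, target 10 points at 24 weeks, 2.5 points per 6 weeks, 200 participants, 10% dropout. From Quality of Life: subscale maxima 21, 18, 9 and 9, items scored 0-3, maximum 57. From Study design: two care units per organization, one in each arm, hence 100 participants per arm.

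**The plan's own figures.**
- Slope: 24/6 = 4 intervals and 4 × 2.5 = 10. Consistent.
- Dropout: 200 × 10/9 = 222.2, so 223 when rounded up. Rounding up per arm gives 100 × 10/9 = 111.1, so 112, and 2 × 112 = 224. The stated 224 is acceptable.
- The 200: alpha, power and intracluster correlation (ICC) are not in the article and are assumed here. SD = √300 = 17.32. A simple comparison at 24 weeks, two-sided 5%, needs n per arm = 2(z₀.₉₇₅ + z_power)² × 300/10². That is 48 per arm (96 in all) for 80% power and 64 per arm (128 in all) for 90%. With design effect 1 + 9 × ICC, 100 per arm is reached when 100/48 = 2.08, so ICC ≈ 0.12 (80% power), or 100/64 = 1.56, so ICC ≈ 0.06 (90% power). The 200 is plausible for the pilot score but can be neither confirmed nor refuted.

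**Mean against scale.** 21 + 18 + 9 + 9 = 57, which matches the stated maximum and 57/3 = 19 items. The 57 is therefore not a slip in one number. 80 − 57 = 23, and 80/57 = 1.40.

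**Variance against scale.** A score bounded by 0 and 57 with mean m has variance at most m(57 − m): 40 × 17 = 680 at mean 40, and 45 × 12 = 540 at mean 45. So 300 is possible on 0-57. It would, however, exceed the variance of a uniform spread over all scores from 0 to 57, (58² − 1)/12 = 280.

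**What a change of scale could do.** Suppose the pilot score ran from 0 to M. A mean of 80 with variance 300 requires 80(M − 80) ≥ 300, so M ≥ 83.75. Shrinking the pilot figures in proportion by 57/M, for assumed M:

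| M | mean | SD | 10 points becomes | standardised effect | effect if 10 points is kept |
|---|---|---|---|---|---|
| 100 | 45.6 | 9.87 | 5.70 | 5.70/9.87 = 0.58 | 10/9.87 = 1.01 |
| 120 | 38.0 | 8.23 | 4.75 | 4.75/8.23 = 0.58 | 10/8.23 = 1.22 |

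On the pilot score the standardised effect is 10/17.32 = 0.58. Proportional shrinkage leaves it, and the sample size, unchanged. Keeping 10 points raises it.

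**When scaling is not proportional.** Dropping subscales need not shrink the SD and the relevant difference together. Assumed values, 100 per arm, 10 per unit, two-sided 5%, comparison at 24 weeks (simpler than the planned slope model):

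| Difference | SD | Power at ICC 0 | Power at ICC 0.20 |
|---|---|---|---|
| 10 | 12 | >99% | 94% |
| 5 | 8 | 99% | 75% |
| 5 | 12 | 84% | 42% |

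Power can move either way, depending on figures the article does not give for the 0-57 score.

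**The case against.** The best defence accepts that 80 is impossible on 0-57 and denies that much follows from it. Only the mean is proven wrong. A variance of 300 and a difference of 10 points can both occur on 0-57, and the mean does not enter the sample size. The 10 points are called a difference on the total score and are not attributed to the pilot. No longer version of the questionnaire is described, and a rescaled score or an error in the figure is not excluded.

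Most of this stands, and it limits the point. A reader might infer that the 10-point target and the 200 certainly belong to a longer questionnaire. The text does not establish that: the link is strong for the variance, which is reported with the mean as pilot data, and weaker for the 10 points. A reader might also infer that the trial is underpowered. The documents do not support that either, since proportional shrinkage leaves the standardised effect at 0.58 and keeping 10 points would increase power.

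The defence does not remove the contradiction. Nor is this a detail that a condensed article may leave to the full protocol, because two published statements about the primary endpoint disagree. By contrast, the absence of variance components, alpha, power and ICC is ordinary condensation and is not part of the point.

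**Conclusion.** The Sample size section is wrong as written. It claims to use the primary outcome but gives a mean 23 points (40%) above that outcome's maximum. This needs no assumption beyond the article's own definition of the score.

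That the variance of 300 belongs to the same other score is very probable. That the 10 points do is possible but unproven. Hence 200 (224 with dropout) is not shown to be right for the 0-57 outcome, and the 10-point threshold cannot be applied to that outcome until its scale is stated. Whether 200 is too many or too few cannot be determined from the article. The power figures above rest on assumed SDs, differences and ICCs and show only that the direction is open. The point should be corrected because it concerns which score is primary and the only stated basis for the sample size.

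**What to change.** State in Sample size which score the mean of 80, the variance of 300 and the 10 points each refer to. Then take one of two routes.

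- **If the four-subscale 0-57 score is primary:** restate its mean, variance and relevant difference. Use the pilot data if subscale scores are available; otherwise give stated assumptions with a range. Rerun the simulation with the mixed model in Statistical analysis, and report the power or detectable difference at 200. No extra enrolment is asked for.
- **If the pilot total was the intended primary outcome:** correct the Quality of Life section to name that total and its range, and reconcile this with that section's statement that not all subscales suit severe dementia.

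The first route costs one simulation run, a short re-analysis of pilot data if the subscale scores exist, and a few replaced sentences. The stated power may turn out less favourable. The second route needs no new simulation for the change of scale, but it rewrites the published definition of the primary outcome and must justify the added subscales.

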### Covariates

Participants’ characteristics that might be of influence are taken into account. These covariates are age, gender, educational level, and ApoE4 status.

The highest educational level is classified by the Verhage scale [31]; a seven point rating scale. A score of 1 equals a level of less than six years of elementary school; score 2 stands for completed elementary school; a score of 3 indicates more than six years of elementary schools and less than three years of secondary education; score 4 is indicative of elementary school and three years secondary education; score 5 stands for elementary school and four years of secondary education; score 6 represents pre-university education and/or higher vocational education; and a score of 7 stands for a finished training at a university or technical college.

Genetic susceptibility for dementia as indicated by ApoE4 genotype, is assessed by collecting buccal cells. Two Catch-all TM collection swabs (Epicentre, Madison, Wisconsin, USA) per participant are used.

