#### Cognition

Cognition, especially memory and executive function, is investigated using a pen-and-paper-based neuropsychological assessment. Trained examiners, blind for the intervention, will visit the participants at the care unit. First, the participant is screened with the MMSE. Based on the MMSE score, a set of neuropsychological tests will be conducted. If a participant is not able to give a single adequate response on any of the MMSE questions (i.e. MMSE score is zero) no further cognitive testing will take place. Participants scoring 1-4 on the MMSE will take the first four tests described below, and participants scoring 5 or higher on the MMSE will perform these tests and three additional tests (also described below). All these tasks are complementary as they assess different cognitive skills.

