### Statistical analysis

The data from this prospective longitudinal matched cluster randomized single-blind multicenter study will be analysed using a linear mixed model. The fixed effects are *‘condition’* and *‘time’*; the linear ‘*condition x time’* interaction is the effect parameter of interest and *‘care unit’* and *‘participant (within the care unit)’* are the random effects (both intercepts and slopes). An intention to treat analysis will be performed.

The baseline (cross-sectional) data will also be analysed for Pearson’s and/or Spearman’s coefficients, to establish correlations between the primary outcome variable QoL and the secondary outcome variables (viz., cognition, mood, independence, rest-activity rhythm, blood pressure, and masticatory function). Additionally, linear regression analyses will be performed to study the independent contribution of the various secondary outcome variables to QoL.

A baseline comparison will be performed to make sure that the intervention group and control group are similar with regards to variables that are not of primary interest (i.e. the covariates and confounders) and the outcome variables. Any difference between the groups afterwards is then likely due to the intervention. If there are differences between the groups prior to the intervention, the baseline scores will be incorporated as covariates in the analysis.

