## Discussion

The described study is a prospective longitudinal matched cluster randomized single-blind multicenter study, investigating the effect of an intervention aimed at increasing masticatory activity by increasing and improving oral health care and the consistency of the diet. Participants in this study are elderly people suffering from dementia and receiving institutionalized care. The intervention is performed by daily nursing staff.

Strengths of this design are the direct clinical applicability of results; a transfer to the clinic does not need to be made since all work is done in a clinical setting. The intervention is performed by the nursing staff, allowing immediate assimilation into daily care. By taking baseline measurements and also repeated follow-up assessments, a thorough insight into the effect of the intervention is obtained. Chance findings are less likely to occur, and the effect over time can be made clear. The broad spectrum of data collection allows for a further widening of the research scope. Besides QoL, important variables such as cognition, mood, independence, and the rest-activity rhythm are assessed. Also, the research methods are varied; both qualitative and quantitative measures are used. By combining these two research methods, we obtain both quantitative, objective data about ‘how’ the intervention is effecting the outcome variables and qualitative, more subjective data, which is descriptive and can provide insight into the ‘why’ an intervention does or does not have an effect. Quantitative data can provide insight in effect sizes and underlying mechanisms, is not subject to interpretation and not dependent on a proxy’s mood and cognition (e.g., [13]). Nonparametric testing, used for qualitative data, is stricter and therefore if results are found, they tend to be more robust. The heterogeneity of the research population is (partly) eliminated by matching and cluster randomizing the care units.

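### The primary model has no prespecified term for dementia severity; baseline MMSE can enter only after an observed group difference, and with no time interaction to bear on the slope contrast

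*Protocol article*

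**What the plan says.** The Participants section of the protocol article excludes an MMSE of 25 or more and sets no lower limit. The Cognition section provides for scores down to zero. MMSE is measured on everyone before the other tests: "First, the participant is screened with the MMSE".

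The Covariates section fixes the list: "These covariates are age, gender, educational level, and ApoE4 status". Severity is not on it.

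The Statistical analysis section gives the primary model. Its fixed effects are condition and time, and the linear condition x time "interaction is the effect parameter of interest". Care unit and participant within unit have random intercepts and random slopes. The listed covariates are given no stated place in this model.

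The same section compares the arms at baseline on covariates, confounders and outcome variables. Cognition is an outcome, so MMSE is among them. It then sets the rule: "If there are differences between the groups prior to the intervention, the baseline scores will be incorporated as covariates in the analysis".

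**The concern.** Severity may well influence how fast quality of life changes, and rate of change is what the trial compares. The article itself links severity to the outcome: it counts mental function as part of quality of life, and it drops Qualidem subscales that do not suit severe dementia.

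Two features of the plan work badly together.

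- The only route for severity into the model is triggered by the observed data, with no stated criterion for what counts as a difference.
- If the rule is triggered, baseline scores become covariates with no time interaction. Such a term addresses differences in level, while the effect parameter is a difference in slope.

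So if the few randomised units happen to differ in severity, the plan as written notices this but does little about it in the comparison that matters.

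**Working it through.** **Inputs from the article.** 10 organisations x 2 units x 10 participants = 200 (Sample size). Visits are at 0, 6, 12 and 24 weeks (Study design). The target is 10 points at 24 weeks, or 2.5 per 6 weeks, with total variance 300 (Sample size). The article gives no figure for the effect of severity and no split of the variance, so the components below are assumptions.

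**Variance of the contrast.** Count time in 6-week steps: 0, 1, 2, 4, with mean 1.75. Then Sxx = (0 + 1 + 4 + 16) - 4 x 1.75² = 21 - 12.25 = 8.75. With complete data at common visits,

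Var(slope difference) = (2/10) x [unit slope variance + (participant slope variance + residual variance/8.75)/10].

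**Step 1: a main effect.** No intercept variance appears in this formula. A severity main effect explains intercept variance only, so it cannot change the result. An exact generalised least squares calculation over six assumed variance splits agrees. For example, take participant slope variance 4, unit slope variance 1 and residual variance 90. The formula gives (2/10) x [1 + (4 + 10.286)/10] = 0.4857, a standard error of 0.6969. Adding a severity main effect that explains 10%, 30% or 50% of the participant intercept variance leaves 0.6969. The other five splits are also unchanged to four decimals. Missing visits make this approximate.

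**Step 2: chance imbalance.** Treating the 20 units as unpaired, the SD of the arm difference in mean unit severity is sqrt(2/10) = 0.45 between-unit SDs. With within-pair correlation r it is sqrt(2(1 - r)/10), so 0.45 is the ceiling for r ≥ 0. For example, r = 0.5 gives 0.32.

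To express this in outcome points, assume total participant slope variance 4 to 9, severity explaining 10% to 30% of it, and severity ICC by unit 0.1 to 0.3.

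- Weakest case: the severity part is 0.4, split into 0.04 (unit) and 0.36 (participant). The SD of the shift is sqrt(0.2 x (0.04 + 0.036)) = 0.123 per 6 weeks, or 0.5 points at 24 weeks.
- Strongest case: the severity part is 2.7, split into 0.81 and 1.89. The SD of the shift is sqrt(0.2 x (0.81 + 0.189)) = 0.447 per 6 weeks, or 1.8 points at 24 weeks.

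Both are for unpaired units, against a target of 10 points.

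**Step 3: gain from severity x time.** The quantity compared is the bracket in the formula, before and after removing the severity part. The weakest case uses residual variance 150 and the others use 100.

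| Assumed setting | Before | After | SE ratio |
|---|---|---|---|
| Weakest case, no other unit slope variance | 2.150 | 2.074 | 0.98 |
| Strongest case, no other unit slope variance | 2.772 | 1.773 | 0.80 |
| Strongest case, other unit slope variance 1 | 3.772 | 2.773 | 0.86 |
| Strongest case, other unit slope variance 4 | 6.772 | 5.773 | 0.92 |
| As strongest, severity not clustered, no unit slope variance | 2.043 | 1.773 | 0.93 |

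The least squares calculation had unit slope variance present (0.1 to 9) and severity not clustered. The standard error fell by 0-2% when severity explained 10% of participant slope variance, and by 0.3-5.6% when it explained 30%. The largest fall was 0.6969 to 0.6577, and power rose by at most about 2 percentage points.

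**Step 4: cost if severity is irrelevant.** In the same calculation the standard error rises by about 0.1%, for example from 0.5952 to 0.5959.

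**Scale.** The planning mean of 80 exceeds the 57-point maximum that the article gives for the four-subscale Qualidem score. Absolute standard errors, points and power are therefore illustrative. The SE ratios depend only on the relative size of the variance components, and step 1 does not depend on them at all.

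**The case against.** The strongest reply is that nothing here is broken. Units are randomised, and the model has random slopes for unit and participant, so chance severity differences are already in the standard error. The Statistical analysis section does not shut severity out, since MMSE is among the variables compared at baseline. Pairing within an organisation should reduce imbalance below the unpaired figure. The choice of prognostic covariates is often left to an analysis plan that is not shown. The article has no figure for how strongly severity predicts slope.

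Most of this stands. No bias is shown, the pairing argument makes 0.45 a ceiling, and the gain rests on assumptions. Two parts do not stand. The article is not silent: it fixes a covariate list, the model's fixed effects and a conditional rule. And that rule does not reach the effect parameter, because by step 1 a baseline covariate without a time interaction leaves the slope contrast essentially where it was.

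A reader might infer that leaving severity off the covariate list by itself costs precision. It does not. The listed covariates have no stated place in the primary model, and as main effects they would not change the slope standard error.

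A reader might also infer a gain of about 20%. That needs severity to be strongly clustered by unit and to be the only source of unit slope differences, whereas the article specifies random slopes for care unit.

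**Conclusion.** The point holds as a low-cost improvement in prespecification. The primary model has no severity term. The only route in is data-dependent, and it would leave the condition x time contrast essentially unchanged. Chance imbalance between 10 and 10 units is the main reason to act, with an SD of at most about 0.45 between-unit SDs and less if matching works. The gain from a prespecified MMSE x time term is about 0-6% of the standard error if severity is not clustered by unit. It is up to about 14% if severity is clustered and some other unit slope variance exists. Both ranges rest on assumed variance splits and on severity explaining 10-30% of participant slope variance.

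Two further readings are not supported. Dementia subtype does not need the same treatment: it is recorded only conditionally ("If possible, the subtype of the dementia disorder"), and no gain from it has been quantified. Nor is the Discussion sentence "The heterogeneity of the research population is (partly) eliminated by matching and cluster randomizing the care units" an error to correct. It is hedged, pairing does remove differences between organisations, and the sentence determines no analysis.

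**What to change.** In the Statistical analysis section, state that baseline MMSE and baseline MMSE x time are fixed effects in the primary model regardless of any observed baseline difference. Add baseline MMSE to the list in the Covariates section so that the two sections agree. The change to the list alone would achieve nothing; the time interaction is the part that matters. No subtype x time terms are needed.

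The data are already collected. The cost is one or two degrees of freedom, and about 0.1% of the standard error if severity does not predict slope.
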